**Figure 1 figure1:**
[figure not shown]
Study flowchart.

#### Part 3: Memory Clinic Visit

All professionals involved in the memory clinic will be blinded to the results of the TYM and SAGE. The visit to the memory clinic will take half a day and will consist of a standardized memory clinic workup.

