### Objectives

Our overall aim is to establish a reliable, valid, and efficient stepped diagnostic procedure to detect undiagnosed cognitive impairment in patients ≥70 years of age with type 2 diabetes. The procedure will consist of a self-administered cognitive test and an evaluation by a GP. Additionally, we will describe how early detection of cognitive impairment affects treatment and quality of life in participating patients in a parallel observational study. The specific objectives of the study are (1) to assess the validity of two self-administered cognitive tests (TYM and SAGE) in detecting undiagnosed cognitive impairment in elderly patients with type 2 diabetes in a primary care setting and to select the best instrument, (2) to assess the diagnostic accuracy of a standardized evaluation by a GP in detecting undiagnosed cognitive impairment in patients with type 2 diabetes, (3) to estimate the accuracy and efficiency of the best cognitive test(s) combined with the evaluation by the GP, and (4) to describe the effect of the diagnostic procedure on several aspects of diabetes care (ie, treatment targets and appointment schedules) and patients’ quality of life.

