### The Diagnostic Strategy

#### Part 1: Home Visit

Participants will be visited at home by a research physician (a trainee GP). The home visit will take about 1 hour. The participant will be asked to fill out the TYM, SAGE, and a questionnaire assessing health status and depressive symptoms, including the Short Form Health Survey (SF-36)[15], EuroQol (EQ)-5D and EQ-VAS [16], and the Center for Epidemiologic Studies Depression Scale (CES-D) [17]. The research physician will be blinded for the scores on the TYM and the SAGE, and will not provide any assistance in filling out the questionnaires. Following the questionnaires, the research physician will administer a standardized diagnostic interview based on the Dutch guideline for case finding of dementia by GPs to both the participant and (if possible) a close informant [18], representing the evaluation by the GP. The interview will include demographic variables, educational level, and living conditions, as well as a medical history and a list of cognitive complaints (Table 1). After the interview, the MMSE will be administered. The MMSE consists of 11 tasks including the domains orientation in time (5 points), orientation in space (5 points), registration of three words (3 points), concentration and calculation (5 points), recall of three words (3 points), language (8 points) and visuospatial abilities (1 point). The maximum score is 30 points with a higher score indicating a higher level of cognitive functioning. A score of ≤24 is suggestive of dementia.

Based on the history taken, the research physician will decide whether the participant should be classified as "suspected of cognitive impairment" or "no cognitive impairment" according to the criteria for MCI and dementia [19,20]. If the MMSE score is ≤24, the participant will always be classified as "suspected of cognitive impairment".

**Table 1 table1:** List of questions about acquired cognitive symptoms for the participant and informant.

Questions		Patient^a^	Informant^a^
Do you have memory problems?			
Do other people think you are forgetful?			
Do you forget names of relatives or peers?			
Do you often lose things?			
Do you have to write more things down to remember it than you were used to?			
Are there activities you stopped doing in the past five years (and why)?			
Do you visit friends or family less often?			
How does cooking, grocery shopping and the household go?			
Do you have trouble managing your finances?			

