### Cognitive Impairment Diagnosis

Within two weeks of the visit to the memory clinic, a multidisciplinary team meeting will be planned with a neurologist, the neurology resident, and the neuropsychologist to establish the diagnosis. Cognitive impairment ( ie, MCI or dementia) is our primary outcome. For the diagnosis of dementia, the DSM-IV criteria will be used [19]. In short, dementia will be defined as memory impairment and impairment in at least one other cognitive domain, including aphasia, apraxia, agnosia, and executive functioning, that significantly affects social or occupational functioning compared to the previous level of functioning, and that is not caused by a delirium. MCI will be diagnosed according to the criteria by Winblad et al, and defined as not normal, not demented, with cognitive complaints that can be objectified by a neuropsychological assessment and/or evidence of decline over time, and preserved basic activities of daily living [20]. In addition, the presumed etiology of dementia will be specified (eg, Alzheimer’s disease).

Guided by the diagnosis, tailored treatment advice will be given to the participants’ GP regarding management of the diabetes treatment and cognitive impairment. Advice for the diabetes treatment will consist of re-evaluation of the proper glycemic target and the risk of insulin treatment. As well, advice evaluating the need for extra support for participants unable to meet treatment goals or in need of tools, for example a memory aid for appointments or medication, will be provided.

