### Statistical Analysis

The diagnosis of cognitive impairment (MCI or dementia) at the memory clinic will be used as the reference standard. To address the first two objectives, participants will be classified as true positive, false positive, false negative, or true negative separately for the evaluation by the GP, TYM, and SAGE.

Not all of the patients in our study will receive the reference standard, which could lead to partial verification bias [25]. However, if only patients with the reference standard were included in the analysis (complete case analyses), the results would be biased because the selection of the patients with the reference standard will not be at random [25]. A reliable method to reduce this bias is to impute the reference standard [25]. A cognitive impairment diagnosis (yes or no) in the memory clinic will, therefore, be imputed for patients who did not attend the memory clinic. Imputed databases (N=10) will be generated with the predictors TYM, SAGE, MMSE, GP evaluation, as well as age, gender, educational level, living situation, and score on the domain mobility of the EQ-5D. The latter two are chosen because they can influence why some patients did not attend the memory clinic. With these imputed numbers, the sensitivity, specificity, positive predictive value (PPV), and negative predictive value (NPV) will be calculated.

The extent to which the cognitive tests and the evaluation by the GP discriminate between participants with and without cognitive impairment will be determined by the area under the receiver operating characteristic (ROC) curve. Next, the optimal cutoff values of the tests for this population will be determined according to the best combination of corresponding sensitivity and specificity assessed with the Youden index. The Youden index measures the effectiveness of a diagnostic marker and enables the selection of an optimal cutoff point [26]. By means of the ROC curve and the best combination of diagnostic values, the optimal instrument will be selected.

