For assessing the accuracy and efficiency of the diagnostic procedure (ie, the cognitive test combined with history taking; objective 3) the results of the best cognitive test and the evaluation by the GP will be combined. This should reflect the future implementation of the stepped diagnostic procedure, in which a GP will only evaluate those patients with a positive test result. Participants will be categorized in the “test positive” group when both the best cognitive test and the evaluation by the GP are positive. This combination will likely have a higher PPV than the cognitive test or the evaluation by the GP alone, leading to a more efficient diagnostic procedure. The added value of the GP’s evaluation will be assessed by calculating the adjusted ROC curve and the net reclassification index [27].

The fourth objective of this study will be addressed by comparing the difference in health status and depressive symptoms between those with and without a diagnosis of cognitive impairment, both at baseline and at the 6- and 24-month follow-up, taking into account potential baseline differences of relevant parameters. In addition, we will describe the changes that were made in diabetes care by comparing the diabetes management before and after study participation (ie, changes in treatment, number of hypo- or hyperglycemic events, emergency and hospital visits).

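### The memory clinic is blinded to TYM and SAGE but not to the GP evaluation or MMSE, so the measured accuracy and added value of the GP step are open to upward bias

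*Protocol article*

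**What the plan says.** The Protocol article's section Part 3: Memory Clinic Visit sets the blinding rule for the assessors of the reference standard: "All professionals involved in the memory clinic will be blinded to the results of the TYM and SAGE". It names no other test.

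The GP evaluation is nevertheless under test:

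- Objective 2 is "to assess the diagnostic accuracy of a standardized evaluation by a GP in detecting undiagnosed cognitive impairment in patients with type 2 diabetes".
- Under Statistical Analysis, "participants will be classified as true positive, false positive, false negative, or true negative separately for the evaluation by the GP, TYM, and SAGE".
- For objective 3, participants enter the test-positive "group when both the best cognitive test and the evaluation by the GP are positive".
- "The added value of the GP’s evaluation will be assessed by calculating the adjusted ROC curve and the net reclassification index".

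The MMSE belongs to this index test. Part 1: Home Visit says "If the MMSE score is ≤24, the participant will always be classified as" suspected of cognitive impairment.

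The reference diagnosis is a consensus judgement. Under Cognitive Impairment Diagnosis, "a multidisciplinary team meeting will be planned with a neurologist, the neurology resident, and the neuropsychologist to establish the diagnosis".

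**The concern.** If those who set the reference diagnosis know an index test's result, the diagnosis can be drawn towards it (diagnostic review bias). The protocol guards against this for TYM and SAGE but not for the GP evaluation, so the exposure is one-sided.

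Borderline MCI is where this matters most. The MCI definition starts from cognitive complaints, and the home visit collects complaints from participant and informant. The research physician also classifies by the same MCI and dementia criteria as the clinic. Sharing criteria is proper, since an index test should target the same condition. It does mean that a known GP classification would reach the team as a ready-made answer to its own question.

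At stake are the accuracy of the GP evaluation (objective 2), the stepped procedure (objective 3), and the adjusted ROC curve and net reclassification index meant to show what the GP adds. None of the analyses described could remove the bias afterwards.

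**Working it through.** **1. Do the other safeguards close the gap?**

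| Safeguard | Section | What it controls | Covers clinic knowledge of the GP result? |
|---|---|---|---|
| Research physician blind to TYM and SAGE | Part 1: Home Visit | Independence of the GP evaluation from the two tests | No |
| Independent physician selects for referral | Part 2: Selection Criteria | Who selects | No; what the clinic is sent is not stated |
| Research physician not told clinic results | Part 2: Selection Criteria | Learning by the home-visit physician | No; opposite direction |
| Clinic blind to TYM and SAGE | Part 3: Memory Clinic Visit | Clinic knowledge of two index tests | No; GP evaluation and MMSE not named |

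The article describes blinding at four points, so the short list in Part 3 reads as a rule and not only as condensation.

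**2. How many diagnoses depend on the clinic?** The plan's own figures reproduce:

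- Test positives: 1.65² × 0.64 × 0.36 / 0.11² = 51.84, rounded up to 52.
- Suspected group: 52 × 1.5 = 78.
- Screen-negatives: 513 − 78 = 435, of whom 65 are sampled (65/435 = 14.9%).
- Seen at the clinic: 78 + 65 = 143.
- Diagnoses left to imputation: 513 − 143 = 370, and 370/513 = 72%.

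GP evaluation and MMSE are both imputation predictors. Any pull towards the GP result in the 143 observed diagnoses would carry into the 370 imputed ones. Blinding does not enter the sample-size formula, so 513 is unaffected.

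**3. How large could the bias be?** The article gives no accuracy for the GP evaluation and no rate of influence, so both are assumed here. Prevalence is the plan's 8%. Let w be the share of diagnoses discordant with the GP result that are switched to agree with it:

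- TP′ = TP + w·FP and FP′ = (1 − w)·FP
- FN′ = (1 − w)·FN and TN′ = TN + w·FN
- Sensitivity = TP′/(TP′ + FN′); specificity = TN′/(TN′ + FP′); PPV = TP′/(TP′ + FP′)

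Worked case per 1,000 people, with true sensitivity 70% and specificity 90%: TP = 56, FN = 24, FP = 92, TN = 828. At w = 20%, TP′ = 56 + 18.4 = 74.4, FN′ = 19.2 and FP′ = 73.6. Sensitivity = 74.4/93.6 = 79.5%, and PPV = 74.4/148 = 50.3%.

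| Assumed true sens./spec. | w | Apparent sensitivity | Apparent specificity | Apparent PPV |
|---|---|---|---|---|
| 70% / 90% | 0 | 70.0% | 90.0% | 37.8% |
| | 5% | 72.7% | 90.5% | 40.9% |
| | 10% | 75.1% | 90.9% | 44.1% |
| | 20% | 79.5% | 91.9% | 50.3% |
| 79% / 95% | 0 | 79.0% | 95.0% | 57.9% |
| | 5% | 80.4% | 95.2% | 60.0% |
| | 10% | 81.8% | 95.5% | 62.1% |
| | 20% | 84.3% | 96.0% | 66.3% |

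Under this mechanism every measure rises for any w above 0 and is unchanged at w = 0. At w = 20% the PPV gain is 12.5 points in the first setting (50.3 − 37.8) and 8.4 in the second (66.3 − 57.9). For scale, the plan's sample-size margin for PPV, set for the SAGE, is 11 points. The model treats the whole cohort alike, so it assumes that imputation passes on the same pull.

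**4. What happens to the combination?** Among people positive on both the test and the GP evaluation, switched non-cases become true positives, so PPV rises. Sensitivity of the combination has no fixed direction. GP-negative cases relabelled as normal leave the denominator, but GP-positive, test-negative people relabelled as cases count as misses.

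**The case against.** The strongest reply is that silence on blinding is not disclosure. No section says that the clinic receives the research physician's classification, interview or MMSE. The clinic has its own inputs: a diagnostic interview, neurological examination, CAMCOG, caregiver instruments, a 90-minute neuropsychological battery and MRI. The home-visit findings are not listed among them. The MCI criteria require complaints to be objectified by neuropsychological assessment and/or shown by decline over time, so the diagnosis does not rest on complaints alone. The full protocol may also specify the referral letter.

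Most of this stands, and it limits what can be claimed. A reader might infer that the GP step's accuracy will be inflated, or inflated by a known amount. The documents support neither, since w = 0 is not excluded. Nor do they support saying that every accuracy measure of the stepped procedure would rise.

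Referral status needs separate treatment. A random screen-negative is by definition negative on TYM and SAGE, so a strict reading of the existing rule already argues against telling the clinic. Knowing only that someone was suspected would not show which of the three tests was positive, so that knowledge would not specifically favour the GP step.

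The reply does not supply the missing protection. One of three index tests, judged by the same team, is left out of the stated rule.

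**Conclusion.** The point holds as an open risk. The stated rule blinds the reference-standard team to two of three index tests, and no other safeguard in the article governs what the team knows of the third. The GP evaluation's sensitivity and PPV, and its apparent added value, are open to upward bias relative to TYM and SAGE. In the stepped procedure the exposure is clearest for PPV.

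Whether bias occurs depends on what the clinic is told, which the article does not say. Its size depends on the GP evaluation's true accuracy and the strength of influence, which the article does not give. The illustrative range rests on those assumptions and should not be read as an estimate. The clinic's own workup would probably keep the effect modest but does not exclude it.

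**What to change.** Extend the sentence in Part 3: Memory Clinic Visit along these lines:

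*All memory clinic professionals, including those at the diagnostic meeting, will be blinded to the TYM, the SAGE, the research physician's classification, the home-visit interview and MMSE, and whether the participant was referred as suspected or as a random screen-negative, until the diagnosis has been recorded.*

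The independent physician who already makes the selection can send the same referral text for everyone.

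For participants already seen, record what the clinic knew. Report objectives 2 and 3 by blinding status as a sensitivity analysis, and state any unblinded assessment as a limitation of those objectives. Keep these participants in the main analysis: if none had been blinded to the GP result, excluding them could discard much of a verified group planned at only 143.

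The cost is a protocol sentence and a uniform letter, with no change to the sample size. The clinic forgoes home-visit information until the diagnosis is recorded, but it takes its own history and runs its own tests. Participants or informants may still mention the home visit, so the blinding will not be perfect.

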### Medical Examination

Participants will be examined by a (trainee) neurologist who will perform a diagnostic interview and a neurological examination, administer the Cambridge Cognitive Examination (CAMCOG) [21], and measure body weight, height, and blood pressure. Body mass index (BMI) will also be calculated. In addition, the Disability Assessment for Dementia (DAD) [22] and the Neuropsychiatric Inventory (NPI) [23] will be administered to a caregiver to measure functional abilities of daily living and to assess the presence of neuropsychiatric symptoms.

### Neuropsychological Assessment

A neuropsychologist will administer a 90-minute standardized neuropsychological assessment examining memory, information processing speed, attention and executive functioning, and visuoconstruction. The division in cognitive domains will be made a priori, according to standard neuropsychological practice and cognitive theory [24]. The domain "memory" will be assessed by the subtest Digit Span of the Wechsler Adult Intelligence Scale -Third edition (WAIS-III) , the Rey Auditory Verbal Learning Test (RAVL), and the delayed recall of the Rey-Osterrieth Complex Figure Test (ROCF). The domain "information processing speed" will be assessed by the trail-making test (part A), the Stroop Color-Word Test (parts 1 and 2), and the subtest symbol digit substitution of the WAIS-III. The domain "attention and executive function" will be assessed by the trail-making test (part B; ratio score), the Stroop color-word test (part 3; ratio score), the visual elevator test, a letter fluency test using the letters ‘N’ and ‘A’, and category fluency (animal naming). The domain "visuoconstruction" will be assessed by the copy trial of the ROCF, the Judgment of Line Orientation (JLO), and the
*Visual Object and Space Perception Battery*
(VOSP). Furthermore, the premorbid level of intelligence (intelligence quotient (IQ)) will be estimated by the Dutch version of the National Adult Reading Test (NART). Educational level will be recorded in seven categories and subsequently translated into years of education. Frailty will be examined with the Short Physical Performance Battery (SPPB).

### Additional Examinations

MRI data will be acquired on a Philips 3.0 Tesla scanner using a standardized protocol and consisting of a T2-weighted scan (48 continuous slices, reconstructed voxel size: 0.99 × 0.99 × 3.00 mm^3^), a 3D T1 scan (192 continuous slices, reconstructed voxel size: 1.00 × 1.00 × 1.00 mm^3^), a fluid attenuated inversion recovery (FLAIR) scan (48 continuous slices, reconstructed voxel size: 0.96 × 0.95 × 3mm^3^), and diffusion-weighted MRI data using a single-shot spin echo planar imaging sequence (48 contiguous slices, acquired isotropic voxel size 2.50 mm, 45 isotropically distributed diffusion-sensitizing gradients with a b value of 1200 s/mm^2^, and one b=0 s/mm^2^).

Venous blood samples will be drawn to determine non-fasting blood glucose, HbA1c, blood count, lipid-levels (HDL, LDL, total cholesterol, triglycerides), thyroid function, liver functions, and kidney function.

### Cognitive Impairment Diagnosis

Within two weeks of the visit to the memory clinic, a multidisciplinary team meeting will be planned with a neurologist, the neurology resident, and the neuropsychologist to establish the diagnosis. Cognitive impairment ( ie, MCI or dementia) is our primary outcome. For the diagnosis of dementia, the DSM-IV criteria will be used [19]. In short, dementia will be defined as memory impairment and impairment in at least one other cognitive domain, including aphasia, apraxia, agnosia, and executive functioning, that significantly affects social or occupational functioning compared to the previous level of functioning, and that is not caused by a delirium. MCI will be diagnosed according to the criteria by Winblad et al, and defined as not normal, not demented, with cognitive complaints that can be objectified by a neuropsychological assessment and/or evidence of decline over time, and preserved basic activities of daily living [20]. In addition, the presumed etiology of dementia will be specified (eg, Alzheimer’s disease).

Guided by the diagnosis, tailored treatment advice will be given to the participants’ GP regarding management of the diabetes treatment and cognitive impairment. Advice for the diabetes treatment will consist of re-evaluation of the proper glycemic target and the risk of insulin treatment. As well, advice evaluating the need for extra support for participants unable to meet treatment goals or in need of tools, for example a memory aid for appointments or medication, will be provided.

### After the Diagnosis

The results of the visit to the memory clinic and the treatment advice will be sent to the GPs who will discuss the results with the participant. Subsequently, the GP and the participant will decide together what actions will be taken. Further support by the memory clinic will be available if considered desirable by the GP and the participant.

### Follow-Up

Following the home visit (6 months), participants will receive a follow-up questionnaire, including the SF-36, EQ-5D, EQ-VAS, and the CES-D to evaluate the course of their health status, quality of life, and depressive symptoms. A questionnaire asking whether and how many hypoglycemic events, visits to emergency services, and hospital admissions they experienced will also be included. In addition, participants will be asked whether they regret their participation in the study and whether they would again participate in the study. A second follow-up questionnaire with the same questions will be sent after 24 months.

After the home visit (6 months), the medical records of the participants will be examined to obtain information on the medical history, values of recent diabetes controls (HbA1c, lipids, creatinine, weight, height, blood pressure), complications (hypo- or hyperglycemic events), and visits to emergency services and hospital admissions in the year before and six months after participation in the study.

To further assess the impact of the study on participants’ treatment, GPs of participants that attended the memory clinic will receive a questionnaire 6 months after the evaluation at the memory clinic to assess whether the study led to new insights and whether it changed their treatment plan (Textbox 1).

Follow-up questions for the general practitioner (GP).Did the result come as a surprise to you or did you expect it? And why?Do you agree with the result of the memory clinic? And why?Did you adjust your diabetes treatment or management because of the results? And why?Did the results have consequences for your overall medical treatment of the patient? And why?

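### Event counts for objective 4 come from a 12-month window before and a 6-month window after; compared as raw numbers, an unchanged rate would show as a 50% fall.

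*Protocol article*

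**What the plan says.** Objective 4 is "to describe the effect of the diagnostic procedure on several aspects of diabetes care" and on patients' quality of life (Protocol article, Objectives).

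The data for the care part come mainly from the medical records. The Follow-Up section sets the time of extraction: "After the home visit (6 months), the medical records of the participants will be examined to obtain information on the medical history". The same sentence goes on to recent diabetes control values and complications (hypo- or hyperglycemic events), and ends with "visits to emergency services and hospital admissions in the year before and six months after participation in the study".

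The Statistical Analysis section sets the comparison: "we will describe the changes that were made in diabetes care by comparing the diabetes management before and after study participation". It lists what is compared: "changes in treatment, number of hypo- or hyperglycemic events, emergency and hospital visits".

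The article mentions no event rate, person-time denominator, annualisation or shortening of the look-back to six months.

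A second source of event data is the participant follow-up at 6 and 24 months: "A questionnaire asking whether and how many hypoglycemic events, visits to emergency services, and hospital admissions they experienced will also be included". The home-visit questionnaire, as described, contains the SF-36, EQ-5D, EQ-VAS and CES-D, with no matching event questions.

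**The concern.** A count of events grows with the time over which it is collected. Here the before period is twice as long as the after period, and the measure named for the comparison is a number of events. Taken literally, the two sections together build a reduction into the result.

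The direction of the error matters. The Discussion presents complications and treatment among the aspects of patients' lives on which the diagnostic procedure may have an impact, and hopes that adjusted treatment might prevent treatment-related complications. An artefact that halves the counts points the way the investigators hope to see. It could also hide a real increase in emergency visits or admissions.

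The participant questionnaire cannot serve as a check, because no self-reported baseline count is described. The records are the only described source of counts for the period before.

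**Working it through.** The plan gives no expected count, sample size or power for this comparison, so there is no figure of its own to reproduce. The check is on the windows and the measure.

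**Inputs**
- Before window: 12 months = 1.0 year (Follow-Up).
- After window: 6 months = 0.5 year (Follow-Up). Because the records are read 6 months after the home visit, the after window cannot be longer than this if it starts at the home visit.
- Measure: number of events, with no denominator stated (Statistical Analysis).
- Planned participants: 513 (Sample Size Calculation).
- Underlying event rate: not given. I assume a constant rate L and vary it from 0.1 to 2.0 events per person-year.

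**Step 1: unchanged rate.** Expected count = rate × window length.
- Before: L × 1.0. After: L × 0.5.
- Ratio after/before = 0.5L / 1.0L = 0.50, an apparent change of −50% at every L.
- Illustration at an assumed L = 0.5: 513 × 0.5 × 1.0 = 256.5 events before, and 513 × 0.5 × 0.5 = 128.25 after.

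**Step 2: a rate that really changes.** If the true rate ratio is R, the raw count ratio is R × 0.5.

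| True change in rate | R | Raw count ratio | Apparent change |
|---|---|---|---|
| 20% fall | 0.8 | 0.40 | −60% |
| none | 1.0 | 0.50 | −50% |
| 50% rise | 1.5 | 0.75 | −25% |
| doubling | 2.0 | 1.00 | 0% |

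**Step 3: does a yes/no outcome avoid it?** If the measure were any event against none, with Poisson events, the proportion is 1 − exp(−L × t).
- L = 0.1: 0.095 before, 0.049 after, change −49%.
- L = 0.5: 0.393 before, 0.221 after, change −44%.
- L = 1.0: 0.632 before, 0.393 after, change −38%.
- L = 2.0: 0.865 before, 0.632 after, change −27%.

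The artefact becomes smaller and depends on the rate, but it does not disappear.

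**Step 4: after correction.** With six months on each side the ratio is 0.5L / 0.5L = 1.0. With events per person-year it is L / L = 1.0. An unchanged rate then shows as no change.

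**The case against.** The strongest reply is that neither section commits the analysts to dividing a six-month count by a twelve-month count. Follow-Up describes data collection, and Statistical Analysis gives a list of variables in parentheses. A year of look-back contains the six months before, so a fair comparison can be made without collecting anything more. The article is condensed, and a fuller plan may state the denominator. This stands in part. The 50% artefact is conditional on raw counts being compared, not certain. It does not dispose of the point, because the article states both the windows and the measure, and the two do not fit together as written.

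The reply on scope also stands. The time phrase attaches most clearly to emergency visits and hospital admissions. It reads naturally onto hypo- and hyperglycemic events earlier in the sentence, but not beyond doubt. Treatment changes are in the same list and do not scale with window length in this way.

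A reader might also infer a second fault: that part of the after window falls before the memory clinic's advice reaches the GP, so the window should restart at the advice for those who attend. The article supports the contrast only loosely. GPs of attendees "will receive a questionnaire 6 months after the evaluation at the memory clinic", whereas the records are read from the home visit. But the interval from home visit to clinic is not stated (the only interval given is a team meeting within two weeks of the clinic visit), so the share of the window lost cannot be derived. The point would concern about 143 of 513 planned participants (143/513 = 28%). Objective 4 concerns the whole diagnostic procedure, not the advice alone. Restarting the clock for attendees only would give attendees and non-attendees different windows. I do not make that claim.

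**Conclusion.** The two sections should be reconciled. Read literally, they compare 12 months of events with 6 months of events. An unchanged rate would then appear as a 50% fall (ratio 0.50), a doubling as no change, and a 50% rise as a 25% fall.

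The exact 50% rests on three assumptions: raw counts are compared, the rate is constant, and follow-up is complete in both windows. It does not depend on the size of the rate. It applies with confidence to emergency visits and hospital admissions, and probably to hypo- and hyperglycemic events.

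A reader might infer that the study's results as a whole are at risk, or that the false fall is bound to be reported. The document supports neither. The affected item is a descriptive part of the last of four objectives. The primary outcome is the diagnosis of cognitive impairment, and the accuracy analyses and sample size do not use these counts. The article itself leaves effects on clinical outcomes to a future randomised trial. The severity is low, but the correction is worth making because the error would favour the procedure.

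**What to change.** Add one sentence to the Statistical Analysis section, under the fourth objective, that fixes the comparison in one of two ways:

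1. Equal windows: compare events in the six months before participation with events in the six months after it. This needs the extraction to record event dates, or at least which half of the look-back year each event fell in.
2. Rates: report events per person-year, with each participant's observed time as the denominator. This uses the whole look-back year and allows for participants observed for less than six months afterwards.

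The same sentence should say which date divides before from after, using one rule for all participants, and whether the windows also apply to hypo- and hyperglycemic events.

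The cost is a wording change. No new data items, visits or participants are needed, and the timing of the record extraction can stay as it is.
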